### Data analysis

#### Quantitative approach

The data will be analyzed following the guidelines for Consolidated Standards of Reporting Trials (CONSORT) statements for cluster randomized trials [52]. The trial statistician will remain blinded until the main analyses are complete (i.e., he/she will not be involved in patient recruitment, data collection, and data management). Baseline characteristics will be presented separately for each randomized group. Baseline characteristics will also be presented separately for dropouts and those who complete the study within each treatment group. Descriptive statistics will be used to summarize patient demographics and to assess the baseline clinical characteristics of all study participants.

All analyses will be conducted at the end of the trial because the outcomes may not be readily measured, long follow-ups and multiple interventions are needed for maximum trial efficacy, and there are no severe side effects or other safety issues of concern that may warrant an interim data analysis. However, a sequential data analysis may be conducted during the midterm evaluation for reporting.

The study populations will be analyzed based on the intention-to-treat (ITT) approach to eliminate potential biases associated with nonrandom loss of participants (refusing to continue participating in the trial). Follow-up data will be collected for all participants, regardless of whether they drop out. Compliance for this study is expected to be good; however, missing data may influence the ITT analysis. Multiple imputations and mixed model repeated measures will be used to handle data missing at random.

#### Integrating qualitative and quantitative data

Data analysis for qualitative and quantitative data will be performed separately; however, inferences from both datasets will be used to draw conclusions. Data integration will be conducted using the embedded design approach as described by Palinkas et al. (2011). The qualitative data will help inform some components of the intervention from the outset in refining some features of the mobile application, and during and after the intervention, the post-qualitative data collection will help augment the outcomes of the intervention.

### Addressing sources of bias

#### Qualitative

The interviews will be audio-recorded to ensure accuracy of the data. Data will be coded by multiple team members for consistency. Constant comparison of codes will be performed by two members, and inter-rater reliability will be determined. Data will be triangulated to ensure validity.

#### Quantitative

After enrolment, community health workers will follow up with women on a weekly basis. We anticipate that performance bias will be reduced considering that the outcome is objective, and we also anticipate that detection bias will be reduced by blinding the statistician and data collectors. Providers, community health workers, and patients (pregnant women) will not be blinded because this is not possible due to the nature of the intervention. Selection bias will be eliminated through random assignment. Attrition bias may be likely in the control group because women in the control group may want to drop out of the study or refrain from providing or responding to questions during subsequent visits, especially because they will not be provided any mobile phones. To minimize this bias, we will sensitize the community through stakeholder meetings on the importance of the control group to encourage participation. To control for contamination, e-vouchers will be used, as the women will not be able to sell, misplace, or share their vouchers. Additionally, the use of equity scores as a baseline cutoff for rural or remote rural areas will help to control for contamination, as the health areas are far from each other. Prior to enrolment, the community sensitization, stakeholder meetings, and education programs will be performed to help increase compliance in the control group and prevent women from becoming unresponsive during the trial. We anticipate minimal loss to follow up due to the nature of the exposure (pregnancy) and outcome (antenatal care and skilled birth delivery).

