## Participants

The study is open to women aged 15–49 (with the current report of underage pregnancy ages of < 15, we anticipate adjusting the age to 13–49 years because this age group is not only vulnerable but also at high risk). Participants must also be ≤ 4 months pregnant and fall within the poverty scale of the study. Any comorbidity that is present at the time of the study that has a direct and/or indirect effect on antenatal care or the life of the woman or her unborn child will be treated appropriately as emergencies within the study (in the intervention group). This step will be performed after the randomization of the health areas into intervention and control groups. Participants in both groups will regularly interact with community health workers.

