## Enrolment

Voluntary informed consent will be collected from each study participant after screening for eligibility and randomization of the intervention and control areas. Consent will be obtained with a witness present in either written (language of choice) or oral form (if the participant is not literate). Individuals who are 13–17 years of age will provide consent with the addition of an assent form and a guardian based on context procedures for those within this age group. All participant medical records and personal information will be kept confidential to ensure privacy during the study. Only certified healthcare providers participating in the trial and project leads will have access to confidential records. The other project team members will have access to vital medical information pertaining to the trial, but another private participant information will be inaccessible.

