### Allocation of health areas

Women attending the antenatal clinic and those identified by a community health worker will be screened for eligibility using a poverty assessment scale that will be employed within the study and incorporated into the Magpi data collection software (https://home.magpi.com/). Standard poverty assessment tools [49] will guide the development and adaption of the final tool to be employed. However, the study will consider contextual approaches of identifying those considered “poor” within the respective communities. Community health workers will help in identifying eligible pregnant women but will be blinded to the cutoff poverty scale that will be employed within the study for inclusion. The project team will decide on the cutoff for poverty eligibility, which will be primarily determined and informed by the formative study, taking context into consideration. Those individuals who are eligible and provide informed consent will be allocated to their respective groups by the project lead and/or coordinator. Upon entering the trial, participants will be aware of their intervention because the randomization is performed at the level of the health area, and it will not be possible to blind the participants.

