### Steps in recruitment

Once a woman is identified by a community health worker to be pregnant, she will be asked a series of pre-eligibility questions after providing informed consent using the recruitment text. The woman will be allowed to ask questions to ensure that she has fully understood the project. Once the woman demonstrates an understanding of the informed consent form that will be administered by either the project lead or project coordinator, she will be asked to sign the form. A set of questions will be administered to screen for eligibility in terms of poverty assessment. These questions will be uploaded into Magpi, which will enable the project lead and coordinator to view the responses. For women who are identified by healthcare workers, a community health worker and project coordinator will follow up at home to administer the eligibility questions and to record the GPS location. Once a woman is identified by the project lead and coordinator to be eligible, the participant is reported to the community health worker or provider. Women will be recruited on a weekly basis until the sample size is attained. Once the participants are enrolled, they will be given a unique identifier number by the healthcare provider; in addition, a phone and a solar charger will be assigned to the woman in the intervention areas.

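### Randomising four health areas does not eliminate selection bias when women are identified, screened and consented afterwards by people who know the arm

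*Protocol article*

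**What the plan says.** The claim is in Addressing sources of bias, Quantitative: "Selection bias will be eliminated through random assignment". The same paragraph states "Providers, community health workers, and patients (pregnant women) will not be blinded", and relies on blinding the statistician and data collectors against detection bias.

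Other sections give the order of events and who does what.

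- **Consent.** Enrolment says "Voluntary informed consent will be collected from each study participant after screening for eligibility and randomization of the intervention and control areas". Participants also places a step after allocation ("This step will be performed after the randomization of the health areas into intervention and control groups"), although what that step refers to is not quite clear.
- **Awareness.** Allocation of health areas says "participants will be aware of their intervention because the randomization is performed at the level of the health area".
- **Eligibility.** Allocation of health areas says "The project team will decide on the cutoff for poverty eligibility", guided mainly by the formative study. Community health workers do not know the cutoff. Steps in recruitment has the lead and coordinator view the poverty answers and decide ("Once a woman is identified by the project lead and coordinator to be eligible"). One or other of them also administers consent.
- **Inducement.** A phone and solar charger go to women in intervention areas (Steps in recruitment), with vouchers for antenatal visits, delivery and transport (Intervention and control). Control women pay out of pocket and receive no phone.

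**The concern.** Randomising areas protects one thing: which areas receive the intervention. It has no hold on which women enter the trial within each area if they are recruited once the result is known. If the chance of being approached, of qualifying or of agreeing depends on the arm, the two groups can differ at entry before the intervention has done anything.

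Two things are at stake. The clinical summaries by arm, which the pilot passes to the larger study, could mix differences in recruitment with intervention effects. And a statement that the problem has been eliminated gives the larger trial no reason to measure it or design against it, although informing that trial is the pilot's purpose.

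**Working it through.** The disputed sentence carries no figure, so the check is to set the sections side by side.

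**1. What is randomised.** Stratification and randomization names two health areas in Ndop and two in Bali. Recruitment and follow up agrees: eight community health workers, two per area, gives 8 / 2 = 4 areas. The sample size section also has four clusters.

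**2. When women enter relative to allocation.** Consent follows randomisation of the areas (Enrolment). Enrolment and Steps in recruitment differ on whether consent comes before or after the poverty questions, but that does not matter here. Women are recruited weekly over an eight-month window, know their arm on entry, and in intervention areas are assigned a phone on enrolment. That is possible only if the areas are already allocated.

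**3. Who acts at entry, and what they know.**

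| Step | Who | Knows the arm? |
|---|---|---|
| Identify the woman | Community health workers, providers | Yes, stated |
| Decide poverty eligibility | Project lead and coordinator | Yes, inferred |
| Administer consent | Project lead or coordinator | Yes, inferred |
| Agree or decline | The woman | Yes, stated |

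The inference rests on two facts. The lead and/or coordinator allocate eligible women to their groups, and they present the intervention at community meetings.

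**4. Whether the motive differs by arm.** The intervention is explained to communities and to individual pregnant women, and the material benefits are in one arm only. The bias section itself expects that control women may drop out or stop answering because they get no phone. The same motive can act at entry.

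**5. Whether a stated safeguard closes the gap.**

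- Hiding the cutoff from community health workers limits coaching of answers. It does not hide the arm, govern whom they approach, or bind those who apply the cutoff.
- Data collectors are blinded but start after enrolment.
- The statistician is blinded but works at the analysis.

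None of these governs entry as a whole.

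**6. Antenatal visits.** Women come either from the antenatal clinic or through community health workers. A clinic-identified woman has already attended. Table 1 counts antenatal visits attended and does not restrict them to visits after enrolment. If the clinic-identified share differs between arms by d, one earlier visit each shifts the mean count by d × 1 visit with no effect at all. The document gives no value for d.

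**7. Size.** For a binary outcome the shift is (difference between arms in the share of some type of woman) × (difference in outcome rate between types). Neither factor is in the document, so no size follows.

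**The case against.** The strongest reply is that this is one overconfident word in a descriptive pilot. The clinical outcomes are marked as planned for the larger study and are summarised only by counts, percentages, means and SDs. Feasibility is judged against fixed thresholds, not by comparing arms. The 15-point difference in the sample size section sizes the larger study. All of that stands. A reader might infer that recruitment bias would consume a set part of the 15 points. For example, if 30% of intervention women were marginally poor, with attendance 15 points higher, and no such women entered in control areas, the shift would be 0.30 × 15 = 4.5 points. With 15% it would be 2.25. Those inputs are invented, and the pilot specifies no test at 15 points.

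Much of what is needed is also already planned: baseline characteristics by randomised group, reporting under CONSORT for cluster trials, baseline income, antenatal questions from T0, and the timing of each visit. That stands too. It can reveal an imbalance among enrolled women but cannot prevent one, and it does not show who was screened out or declined.

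A reader might also infer that staff will bend the cutoff in borderline cases, or that it will be set after allocation. The article says neither. Table 2 puts the formative study in June to August 2018, before the study period, so an early cutoff is quite possible. The article gives no date for it, however, and allows contextual approaches to defining poverty within each community. Shaded answers and a different mix of recruitment routes are likewise possibilities, not reported facts.

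Finally, the health area cannot be hidden from a lead or coordinator who meets women in person, so masking them would need other staff. That is correct, and the fix below does not depend on it.

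**Conclusion.** The point holds in a limited form. The protocol claims a property that its recruitment sequence does not provide: randomising four areas guards against biased allocation of areas, not against differential recruitment of women within them. For community health workers, providers and women, knowledge of the arm is stated. For the lead and coordinator it is inferred, but plainly so.

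The size of any bias is unknown and cannot be computed from the document. The conclusion is that recruitment bias remains possible, not that it will occur or that the pilot's feasibility results are invalid. The correction is worth making because the pilot can measure this risk for the larger trial at little cost.

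**What to change.** - **Correct the sentence.** For example: randomisation of health areas guards against biased allocation of areas; because women are recruited after allocation by people who know the arm, differential recruitment remains possible and will be measured in this pilot.
- **Fix the cutoff.** Record the poverty cutoff, with a date, before areas are randomised. Have Magpi, which already takes the answers, apply it by a preset score that is the same in all areas, so that unblinded staff do not make the eligibility decision. If areas have already been randomised, report when the cutoff was set relative to that date and carry the rule into the larger trial.
- **Report the flow.** Give numbers identified, screened, eligible, refusing and enrolled, by area and arm, with baseline poverty score, gestation and recruitment route.
- **Separate antenatal visits.** In any arm comparison, count visits after enrolment or adjust for visits recorded at T0, using the visit data and timing already planned.

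The cost is a scoring rule, a dated record, entry of recruitment route and refusals, and one extra table. The team gives up departures from the preset score. These steps leave untouched whom community health workers approach and who agrees once the benefits are known, so that limit should be stated.

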### Economic data

We will conduct cost minimization evaluations for the intervention to identify feasible and appropriate cost minimization strategies for the project. This information will be used to inform the cost for a transition-to-scale phase. Changes in the resources utilized over time in the district’s health areas relative to the control areas will be calculated and used in conjunction with the costs of setting up and delivering the intervention in the communities. The net cost of program delivery per family will be calculated and will represent the incremental cost of providing the program relative to standard practice.

## Discussion

The outcome of the feasibility project is to introduce an innovative platform for RMNCH delivery called the BornFyne-PNMS project. The paper describes the feasibility study protocol for a cluster randomized control trial to study the effectiveness of e-vouchers and a mobile phone application in selected communities in the northwestern region of Cameroon in improving the access to and utilization of reproductive maternal and newborn child health.

The data collected during this study will allow us to better assess feasibility of the intervention, processes, and resources necessary to scale up and inform a larger trial and how the intervention can boost quality of care. In addition, the results or strategies can also be used by the PBF community to enhance the delivery of care and quality of care indicators, especially as this community is mostly focused on RMNCH. This will then inform policy on specific demand-side strategies that are relevant, especially as this intervention intends to use the PBF platform as a potential platform for sustainability.

### Ethics

Ethical approval for this study has been obtained from the North West regional delegation of health in Cameroon and the University of Ottawa Social Science Ethics board. Administrative clearance has been received from all the district medical officers in the respective districts, the Division for Health Operations Research (DROS) in Cameroon, and the regional delegation for health for the Northwestern region. In addition, administrative approval was also obtained from the Ministry of Public Health at the national level in Cameroon. The trial has been registered with the WHO Pan African Trial Registration.

### Dissemination

The results will be widely disseminated through formal and informal mechanisms. During the post-FGD, meetings will be held by participants to inform them of the results and to obtain their feedback and recommendations. We will inform participants in the control arm regarding the possibility of scaling up if we transition-to-scale. Providers in the control group will be informed about how the intervention will be incorporated into their community and the considerations for the scale up. The study findings will be presented to stakeholders at the district and regional levels and to the ministry of health at the national level in collaboration with the delegation of research (DROS) in Cameroon. The results will be presented to the performance-based financing regional and national offices in Cameroon.

The results will also be presented at regional, national, and international conferences and meetings, as well as presented to the funding agency. Manuscripts will be prepared by the team for submission to peer-reviewed journals, and other strategies will be used to disseminate the results through development agencies, consortia, and innovative competitions.

### Anticipated use of results

We anticipate using the results to inform a larger trial related to effectiveness, as well as to estimate the cost involved to inform a larger phase of the study.

### Limitations

Due to political instability, data and project interruption, delays may be experienced during the project. With the adoption of PBF as a national strategy in Cameroon, the trial may use a pragmatic approach; the proposed non-PBF district may become enrolled into PBF at the time of the intervention.

### Strengths

The team assembled to conduct the feasibility study has experience in designing and implementing mhealth interventions. Second, some of the team members understand the health system in the context of the study. In addition, the study will be implemented within the platform of PBF which provides a pragmatic approach to better inform possible integration of vouchers within the PBF platform for RMNCH. Approval from the district medical officers of the respective pilot districts provides an additional strength for a pilot study.

## Data Availability

All the data sets that will be generated in the study will be available through publications and will also be submitted to the funding agency. In addition, all relevant data will be available and uploaded to the trial registry accordingly.

## Abbreviations

CHW: Community health workers
GIS: Geographic information system
PNMS: Pre-natal management system
PBF: Performance-based financing
RMNCH: Reproductive maternal and newborn child health
